### Blinding

This is a double-blind (patients and clinicians are blinded) and double-dummy study. A two-stage blind design is adopted. The first stage was the group corresponding to number of each case (such as group A, group B) and the second stage was the intervention corresponding to each group (experimental group or control group).

Treatment assignments will not be revealed until the whole process is completed. Emergency letter will be opened by researchers when emergency (such as severe adverse events) or patient needs rescue and must know the treatment had received. Once the blind is broken, the patient with this number will be withdrawn from the trial handling as a dropout case and the researchers should record the reasons in the case report form (CRF). All emergency letters will be returned together with the CRF after the trial for blind review. When the blind codes are leaked or the opening rate of emergency letter exceeds 20%, the double-blind test will declare failure.

To achieve blinding, the outer packaging of experimental and control drugs should be identical. Size, color, shape, taste, smell and packaging of the simulant are identical to that of the corresponding medicine by adding artificial pigment [23].

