### Exit criteria

Patients will leave the trial when one of the following criteria is met:

The symptoms of patients get worse after 3 days of medication;Some comorbidities, complications or special physiological changes occur during the test;Patients with poor compliance don’t reach 80% of the prescribed amount should be used in the trial;Cases breaking the blind or opening the blind urgently in the trial;Drugs out of prescribed protocol are used in the trial;Patients who want to quit the trial or refuse to accept prescription and examination have the right to withdraw from the trial according to the provisions of the informed consent. And the reason should be understood and documented possibly.

Notice: Whatever reason the cases are dropped out of the trial, the CRF should be kept and transformed into final result using the last result examined, and the efficacy and adverse reactions (ADRs) should be carried out using its full data set.

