### Elimination criteria

Patients do not meet the inclusion criteria are founded after enrollment;Drugs out of prescribed plan are used in the trial;Cases no medication after enrollment;Cases no evaluation or record about medication.

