### Discontinuation

Clinical symptoms and signs have no improvement or aggravation compared with those before enrollment after taking the medicine for 3 days or more. That needs to switch to another treatment and stop the medication. After completing the post-treatment evaluation and related laboratory tests, this case is declared over and this patient is recorded in PPS as invalid and qualified case statistics. When the body temperature of patient returns to normal and the symptoms and signs disappear within 5 days, the drug can be stopped. Follow-up visit is conducted after 24 h. If there is no recurrence, it will be counted as a recovered case.

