### Follow-up

All included patients will be re-evaluated after five days of treatment to assess the efficacy and safety. Patients whose symptoms worsened will receive a supply of relevant medicine and a written withdrawal schedule.

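### Emergency unblinding, complications and prohibited drug use take the child out of the trial, and no section clearly assures the assessments still due up to 120 h

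*Protocol article*

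**What the plan says.** The Blinding section lets the emergency letter be opened for an emergency such as a severe adverse event, or when a child needs rescue and the treatment must be known. The consequence is: "Once the blind is broken, the patient with this number will be withdrawn from the trial handling as a dropout case".

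The Exit criteria begin "Patients will leave the trial when one of the following criteria is met". The list includes opened blinds, drugs outside the protocol, worsening after 3 days, low compliance, refusal, and this item: "Some comorbidities, complications or special physiological changes occur during the test". A closing notice covers every reason for dropping out: "the CRF should be kept and transformed into final result using the last result examined". It adds that efficacy and adverse reactions are to be analysed on the full data set.

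The Elimination criteria list off-plan drug use a second time: "Drugs out of prescribed plan are used in the trial".

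Three sections bear on what happens afterwards:
- Discontinuation covers non-improvement or worsening after 3 days or more: "After completing the post-treatment evaluation and related laboratory tests, this case is declared over". For children who recover early it says "Follow-up visit is conducted after 24 h".
- Follow-up says "All included patients will be re-evaluated after five days of treatment to assess the efficacy and safety".
- Safety assessments say that all participants have the listed laboratory examinations, without saying when.

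Table 2 schedules visits at day 0 and at 24, 48, 72, 96 and 120 h. The rows for blood and urine, liver and kidney function, ECG, pathogen and inflammatory factors are ticked at day 0 and 120 h only.

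**The concern.** Stopping a drug and ceasing to be observed are different events, and these rules merge them. The merger matters most where the exit itself carries information. A blind is opened because of a severe event or a need for rescue. A complication is a secondary outcome in its own right and part of the definition of invalid treatment. These are children whose later course a safety and efficacy comparison needs, and they leave because of a rule, not because the family refused.

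If a site follows the text, their data end at exit and the most recent value stands in for the rest. For a time-to-recovery primary outcome that substitution has no clear meaning: a last temperature in a febrile child is not a recovery time.

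**Working it through.** The plan gives no figure for exits by reason, so there is none to reproduce. The check sets the sections side by side and counts what remains on the schedule.

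**Inputs.** Post-baseline visits at 24, 48, 72, 96 and 120 h, so 5 visits (Table 2). Named laboratory, ECG and pathogen tests after baseline: 120 h only (Table 2). Earliest exit for worsening or non-improvement: 3 days = 72 h (Exit criteria, Discontinuation). Compliance check: scheduled at 120 h only (Table 2).

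**Step 1: what an exit at time t leaves open.** Hours left = 120 − t; visits left = scheduled visits after t.

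| Exit at | Hours left | Visits left of 5 | Named 120 h tests |
|---|---|---|---|
| 24 h | 120 − 24 = 96 | 4 | not assured |
| 48 h | 120 − 48 = 72 | 3 | not assured |
| 72 h | 120 − 72 = 48 | 2 | not assured |
| 96 h | 120 − 96 = 24 | 1 | not assured |

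**Step 2: which triggers this reaches.**
- Unblinding, complications and prohibited drugs can occur at any time and have no stated closing evaluation. The whole table applies to them.
- Worsening or non-improvement cannot trigger an exit before 72 h, so at most 48 h and 2 visits are open. Discontinuation requires closing tests for these children.
- Low compliance found at its scheduled check loses 120 − 120 = 0 h.

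**Step 3: does another section restore the assessments?**
- Discontinuation sets closing contacts for non-improvers and for early recoverers. It names none for the three triggers in question.
- Follow-up speaks of all included patients but ties the re-evaluation to five days of treatment. That may mean the 120 h time point or completed treatment. For worsened children it promises medicine and a withdrawal schedule, not assessments.
- Safety assessments cover all participants but give no timing; day 0 tests would satisfy the sentence.
- The section on patient compliance strengthens follow-up for poor efficacy and compliance, without a time or a test, and does not mention the three triggers.
- The general indicator-check row of Table 2 has a 24 h tick but names no test.

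None of these clearly overrides the instruction that the child leaves.

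**Step 4: consequence by outcome.** Unless an unscheduled test is done, a child who exits early for one of the three reasons has no post-baseline laboratory, ECG or pathogen result. A child febrile at exit has no observed primary outcome. For off-plan drug use, the Exit criteria keep the child in the full data set while the Elimination criteria also list the same event, so whether the last result is analysed at all is unsettled.

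**The case against.** The strongest reply is that no sentence says assessments stop, and that a journal article leaves exit procedures to the full protocol. That stands as far as it goes: silence on procedures is not the point. What the article does state is that the child leaves and that the most recent result becomes final, and those statements are the point.

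It may also be said that Follow-up's reference to all included patients extends to non-completers, since its next sentence deals with worsened children. That is a fair reading, but not the only one.

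A further reply is that the 120 h tests cannot be both planned for every child and not assured. They can: the schedule plans them for everyone, and the exit rules let a child drop off it.

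Several stronger readings are tempting and are not supported:
- A reader might infer that normal baseline liver and kidney values become post-treatment safety values. The safety set requires safety data after treatment, and the analysis compares values before and after, so a baseline value does not fit. Nor does any text suggest that a child unblinded for a severe event would go without a blood test.
- A reader might infer that the positive day 0 antigen makes an unblinded child an invalid case. The comprehensive efficacy criteria are judged once medication has ended, which a day 0 test does not meet.
- A reader might infer that any rescue drug forces an exit. The Concomitant section allows antipyretics and analgesics when necessary, and provides for recording medication required by adverse events. Only prohibited drugs count.
- A reader might turn 96 of 120 h into an 80% loss of information. These are clock hours. The planning means are 30.47 h and 46.50 h, so many later exits would follow temperature recovery and cost the primary outcome nothing.

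**Conclusion.** The point holds as a should-fix matter of design. For emergency unblinding, complications and prohibited drug use, the text takes the child out of the trial, makes the most recent result final, and does not clearly assure anything afterwards. Its size per child is 1 to 4 of 5 post-baseline visits for an exit between 24 and 96 h, plus the only scheduled post-baseline laboratory, ECG and pathogen tests. A recovery time is lost only for children still febrile at exit.

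This rests on reading the exit wording as written and on no unscheduled test being done. How many children are affected, and whether the loss favours either arm, cannot be determined from the document. No bias in a stated direction is claimed.

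**What to change.** In Blinding and Exit criteria, and in Discontinuation for children who switch treatment, state that study drug stops but the child stays in the trial. Specifically:
- Continue the temperature, symptom, concomitant drug, adverse event and complication assessments to 120 h, and do the 120 h laboratory, ECG and pathogen tests.
- Reserve withdrawal for refusal of further examination.
- State under Follow-up that the re-evaluation applies whether or not treatment was completed.
- Use observed values instead of the most recent earlier result, and record the dates of stopping and of any new treatment.

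The rules for stopping study drug can stay. How recovery time is handled after a switch of treatment is a separate decision that this change does not settle; it only ensures that the observations exist.

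The cost is a protocol amendment and CRF wording, since the visits and tests are already on the schedule. The downside is more contact with children off study drug: up to 96 h, about 4 days, after an exit at 24 h, and 48 h, about 2 days, after one at 72 h. If the sponsor already intends this follow-up, the amendment merely says so.

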### Eligibility criteria

The diagnostic criteria will be formulated from epidemiological history, clinical manifestations and laboratory diagnosis according to *the Guidelines for the diagnosis and treatment of Influenza (Beijing 2018)* [15].

### Inclusion criteria

Patients get influenza within 48 h with positive results of rapid defection for virus antigen.Apart from general influenza symptoms, patients’ temperature before study is over 38℃;Patients’ age is between 2 and 14 years and informed consents (from guardian or patient themselves) is got.

### Exclusion criteria

Patients is not common influenza (severe or critical) or concomitant other respiratory or pulmonary infections;Patients is not virus infection (mycoplasma infection or bacterial infection);Patients’ laboratory examination results such as serum creatinine (SCR), alanine aminotransferase (ALT) or aspartate aminotransferase (AST) are exceeded the normal range;Patients has severe malnutrition, immunodeficiency (or taking glucocorticoid) or severe vital organ diseases;Patients with severe infections must be treated with other antiviral drugs;Patients are allergic to the RDN or Oseltamivir phosphate granules;Patients has taken Oseltamivir or other heat-clearing & detoxicating traditional Chinese medicine before study;Patients may cause loss of follow-up such as unstable living environment.

Patients with any of the above should be excluded.

### Exit criteria

Patients will leave the trial when one of the following criteria is met:

The symptoms of patients get worse after 3 days of medication;Some comorbidities, complications or special physiological changes occur during the test;Patients with poor compliance don’t reach 80% of the prescribed amount should be used in the trial;Cases breaking the blind or opening the blind urgently in the trial;Drugs out of prescribed protocol are used in the trial;Patients who want to quit the trial or refuse to accept prescription and examination have the right to withdraw from the trial according to the provisions of the informed consent. And the reason should be understood and documented possibly.

Notice: Whatever reason the cases are dropped out of the trial, the CRF should be kept and transformed into final result using the last result examined, and the efficacy and adverse reactions (ADRs) should be carried out using its full data set.

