**Indicator check**						
Temperature	√	√	√	√	√	√
BP/HR/P/symptoms/signs	√	√	√	√	√	√
Blood routine/Urine routine	√					√
Liver function/Kidney function	√					√
Twelve-lead ECG	√					√
Pathogen test	√					√
Inflammatory factor test	√					√

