### Data statistic and analysis

#### Data selection

Four datasets will be conducted intention to treat (ITT), full analysis sets (FAS), per protocol set (PPS), and safety analysis set (SS). ITT is conducted for efficacy and AEs. FAS refers to the ideal set of participants who are as close as possible to the principle of intention to treat and is obtained after removing the participants from all the randomization with the least and reasonable method. PPS, a subset of FAS, is a data set generated from disease case set fully compliant with the trial protocol. SS refers to the randomized cases that have taken a tested drug at least once with safety evaluation data after treatment.

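### Children who leave before 120 h without a retest are given their entry antigen and SCR/ALT/AST values as final results

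*Protocol article*

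**What the plan says.** The notice that closes Exit criteria covers every dropout, for any cause. It says that "the CRF should be kept and transformed into final result using the last result examined", and goes on to say that "the efficacy and adverse reactions (ADRs) should be carried out using its full data set".

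In Table 2, the rows "Liver function/Kidney function" and "Pathogen test" are ticked at day 0 and in the 120 h column only. Blood and urine routine, ECG and inflammatory factors follow the same pattern. There is no early-exit column.

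Entry values are set by eligibility. Inclusion criteria admit patients "with positive results of rapid defection for virus antigen". Exclusion criteria bar those whose "laboratory examination results such as serum creatinine (SCR), alanine aminotransferase (ALT) or aspartate aminotransferase (AST) are exceeded the normal range".

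One type of early stop has its own tests. For a child with no improvement or with worsening after 3 days or more, Discontinuation says: "After completing the post-treatment evaluation and related laboratory tests, this case is declared over".

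The results feed three places: the negative conversion rate (Secondary Outcome measure), cure and invalid treatment (Criteria of comprehensive efficacy), and the before/after laboratory comparison (Analysis contents). Under the comprehensive criteria, cure needs a negative antigen. As worded, a persisting positive antigen is enough on its own to make the case invalid.

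**The concern.** Carrying the last result forward makes sense only if that result says something about treatment. Here, a child who leaves between day 0 and 120 h without a retest has one antigen result and one set of liver and kidney results, all taken before the first dose. Eligibility has already fixed what they show: antigen positive, and SCR, ALT and AST not above normal.

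The rule therefore gives that child a final result that no treatment could have changed, and it pushes two conclusions in opposite directions. For efficacy, the child is a viral failure. For safety, if the carried value is used as the after-treatment value, the child shows no liver or kidney abnormality. If one arm loses more untested children than the other, the difference in exits shows up as a difference in viral clearance.

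The children concerned may be informative ones. Complications are an exit reason, and the Blinding section treats emergency unblinding, for example after a severe adverse event, as a dropout.

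**Working it through.** **Step 1. Which leavers have a stated retest.** The exit reasons in Exit criteria, set against Discontinuation and Table 2:

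| Exit reason | Antigen or laboratory retest stated |
|---|---|
| Worsening after 3 days | Yes, under Discontinuation, though the tests are not itemised |
| Comorbidity, complication, physiological change | None |
| Compliance under 80% | None, but compliance is ticked only at 120 h, so the tests may have been done by then |
| Unblinding | None |
| Off-protocol drugs | None |
| Withdrawal or refusal | None |

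**Step 2. What is carried forward.** Antigen: positive, so not converted, not cured and invalid. SCR, ALT and AST: not above normal. Eligibility does not guarantee normal blood, urine or ECG results at entry, so for those tests the carried value is merely pre-dose.

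**Step 3. How many children.** The plan's own total is reproduced by 200 × 1.20 = 240. Twenty percent of 240 is 48. The room left above 200 is 240 − 200 = 40, or 40/240 = 16.7%. Both are used below.

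**Step 4. Effect on a reported rate.** Let q be the true rate, d the share who drop out and f the share of those with no retest. Assume that q is the same in leavers and completers. Each untested leaver counts as no event, so

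reported rate = q × (1 − d × f).

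The documents give neither q nor f. Taking q = 80% for negative conversion and q = 10% for a new ALT abnormality, both assumed:

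| d | f | Children with day-0 value | Conversion reported (true 80%) | ALT abnormality reported (true 10%) |
|---|---|---|---|---|
| 16.7% | 0 | 0 | 80% | 10% |
| 16.7% | 0.5 | 20 | 73.3% | 9.2% |
| 16.7% | 1 | 40 | 66.7% | 8.3% |
| 20% | 0 | 0 | 80% | 10% |
| 20% | 0.5 | 24 | 72% | 9.0% |
| 20% | 1 | 48 | 64% | 8.0% |

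Example: 0.80 × (1 − 0.20 × 0.5) = 0.72.

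**Step 5. Effect on the arm comparison.** Let u be the untested share (d × f) in an arm. With equal true rates, the spurious difference between arms A and B is q × (u_B − u_A). It is zero when the untested shares are equal. At q = 80%, each percentage point of imbalance produces 0.8 points of apparent difference in conversion.

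**The case against.** Several points against the concern have force.

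- **How many are untested.** A reader might infer that most early leavers receive their entry values. The document does not support this. Exits are not split by reason, non-responders have tests under Discontinuation, and poor compliance may come to light only at 120 h.
- **General statements about testing.** Follow-up re-evaluates all included patients after five days, and Safety assessments says that all participants have the laboratory examination. Either could be read to include leavers. Neither mentions exits, and a last-result rule is needed only where later results are missing, so this stays unclear.
- **The laboratory comparison.** Nothing states that a day-0 value serves as the after-treatment value in Analysis contents. The exit notice names efficacy and adverse reactions. Its use for laboratory shifts is a natural reading, not a stated rule, and an analysis plan could settle it. The safety half of the point is conditional on that reading.
- **The safety set.** It is tempting to add that the definition, "SS refers to the randomized cases that have taken a tested drug at least once with safety evaluation data after treatment", removes untested children, so that they count as normal or not at all. That does not hold. Adverse events and vital signs are recorded every 24 h, so a child who leaves with an adverse event will normally have safety data after dosing. Data selection also uses the ITT set for adverse events.
- **Counting untested children as failures.** This is a recognised conservative choice, and a per-protocol analysis is planned alongside the full set. But treating them as failures protects the arm comparison only if exits are balanced, and the per-protocol set is not a missing-data analysis.

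An article condenses a fuller protocol, which may list exit tests. The point rests on what the article does state: the rule, the schedule and the entry criteria.

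**Conclusion.** The concern holds for one defined group: children who leave before 120 h, for reasons other than the non-response stop, with no test after day 0. The rule as written gives them a pre-dose value as their outcome. Their viral failure is overstated. Liver and kidney abnormality is understated if the rule is applied to the before/after comparison.

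The size cannot be fixed from the document. At 20% dropout it runs from no effect to an assumed 80% conversion being reported as 64%, with 72% if half the leavers are untested. This assumes the same true rate in leavers and completers. Bias between the arms requires unequal untested shares.

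Temperature recovery time, the primary outcome, is outside this mechanism because temperature is measured repeatedly during treatment. What is exposed is a named secondary outcome, the comprehensive efficacy classification and possibly laboratory safety. A test not taken at exit cannot be recovered at the analysis stage.

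**What to change.** 1. In the Exit criteria notice, state that a day-0 value is not carried forward as the final result for antigen or laboratory tests. Report laboratory shifts among children with a post-dose test, and show the number untested by arm and exit reason. Give negative conversion twice: with untested children counted as failures, and with them treated as missing.

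2. Extend the end-of-case tests under Discontinuation to the other exit reasons where consent allows, using the set already planned for 120 h. Add an early-exit column to Table 2.

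The cost is wording in the protocol and analysis plan, with tests already planned for 120 h done at the exit date instead. There is a small downside. Exit tests fall at varying times, and an early antigen test does not measure clearance at 120 h. An arm with more or earlier exits could still show lower conversion if such results were pooled with the others. Exit antigen results should therefore be labelled with their time and not treated as 120 h results.
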